**Condition category**

Chronic tinnitus

**Date applied**

16/05/2021

**Prospective/Retrospective**

Retrospectively registered

**Overall trial status**

Completed

**Recruitment status**

No longer recruiting

**Summary**

Background

About 10-20% of the population has chronic tinnitus and 1% suffers very severely. There is no curative therapy, but there are treatment options that can reduce the burden of tinnitus. Due to a lack of therapists, reduced mobility of many patients and structurally weak rural regions, many sufferers do not get access to therapy. Internet-based therapies could close this health care gap.

Objectives and study aims

This pilot study investigates whether the UNITI smartphone app is a feasible and effective treatment option for chronic tinnitus. The UNITI app consists of structured tinnitus counseling, acoustic therapy and an Ecological Momentary Assessment (EMA) module that measures tinnitus symptoms and well-being on a daily basis. A single-case experimental design (SCED) will be used. During a baseline phase, EMA is used to record symptoms on a daily basis before the treatment modules are additionally introduced in an intervention phase (EMA continues). The outcome variables (tinnitus loudness and distress) will be recorded before the baseline phase and after the intervention phase using clinical questionnaires, as well as during both phases using EMA. On the one hand, treatment compliance and app use is being investigated. On the other hand, it will be investigated whether the tinnitus symptoms are reduced by the app intervention. Participants are of age, have chronic tinnitus and at least a mild tinnitus burden.

Study design

Multiple baseline design across 4 groups (from the group of Single-case experimental designs)

[figure not shown]

- Two phases: baseline phase (only EMA), intervention phase (EMA, structured counseling, acoustic therapy)
- Staggered introduction of intervention phase to separate treatment effects from random time effects and therefore enhance internal validity
- Intervention phase start is determined randomly (criteria: minimum baseline phase duration of 7 days, distance of 3-5 days to each other)
- Intervention phase: 12 weeks for all groups
- Before baseline phase and after intervention phase: clinical questionnaires

Randomization

Participants are randomly allocated to groups; the order of the groups is randomly determined and the start of the intervention phase is randomly determined (Koehler-Levin method)

Inclusion criteria
1) adult (age ≥ 18 years), 2) chronic tinnitus (duration ≥ 6 months), and 3) THI-score ≥ 18 (indicating at least a mild tinnitus handicap)

Exclusion criteria

1) tinnitus-related therapy within the last 3 months and 2) similar therapy with long term effects e.g., noiser.

Target sample size

minimum 20 participants (to allocate at least 5 participants to each group)

Location

The whole study is conducted online.

Outcome measures

There are two different measurement methods: Clinical questionnaire and Ecological Momentary Assessment

Clinical questionnaire (applied before baseline phase and after intervention phase)

- Tinnitus Handicap Inventory (THI)

Ecological momentary assessment (applied daily during baseline and intervention phase)

- Tinnitus distress measured on a visual analogue scale (0 not burdensome – 100 very burdensome): “How burdensome do you find your tinnitus at the moment?”
- Tinnitus loudness measured on a visual analogue scale (0 inaudible – 100 very loud): “How loud is your tinnitus at the moment?”

Intervention

Structured Counseling: Daily information about tinnitus ranging from basics about hearing and tinnitus to more advanced topics such as therapeutic options. Additionally provided tips on how to better deal with tinnitus and weekly quizzes to test knowledge.

Acoustic therapy: Sound library with natural and digital sounds using different filters i.e. therapeutic approaches. Recommendation to use at least 15 minutes per day.

Statistical analysis

- Descriptive statistics for demographics, tinnitus characteristics and app use
- THI: paired t-test to determine change from pre baseline phase to post intervention phase
- EMA: visualization of tinnitus symptom courses (tinnitus distress and loudness)
- EMA: paired t-test to determine change from baseline phase to end of intervention phase
- EMA: change in relationship between tinnitus distress and loudness over study course
- Comparison of THI with EMA tinnitus distress

Timescale

Recruitment and data collection will probably take place between May and October 2021. Afterwards, results will be analysed and written up for publication.

Ethical approval

The study is approved under the ethic vote 20-1936_2-101 „UNification of treatments and Interventions for TInnitus patients – Randomized Clinical Trial (UNITI-RCT)“ (Amendment No. 2) by the ethics committee of the University of Regensburg, Germany.

Funding

This project receives funding from the European Union's Horizon 2020 Research and Innovation Programme, Grant Agreement Number 848261.

Where is the study run from?
University of Regensburg

Primary contact

[name]

[contact]
_____

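### The protocol credits the staggered start with separating treatment from time effects, but its two before-after tests, of THI and of end-of-intervention EMA, do not use the stagger

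*Protocol*

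**What the plan says.** All places are in the Protocol, Summary.

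- **Study design** gives the purpose of the stagger: "Staggered introduction of intervention phase to separate treatment effects from random time effects and therefore enhance internal validity". It describes four groups. The start of the intervention is random within these limits: "minimum baseline phase duration of 7 days, distance of 3-5 days to each other". The length of treatment does not vary: "Intervention phase: 12 weeks for all groups".
- **Randomization** allocates participants to groups at random and adds that "the order of the groups is randomly determined and the start of the intervention phase is randomly determined (Koehler-Levin method").
- **Outcome measures** has the THI at two time points only: "Clinical questionnaire (applied before baseline phase and after intervention phase"). EMA distress and loudness are recorded daily in both phases.
- **Statistical analysis** lists two tests of change: "THI: paired t-test to determine change from pre baseline phase to post intervention phase" and "EMA: paired t-test to determine change from baseline phase to end of intervention phase". The EMA courses are also to be plotted. No listed test refers to group, start point or study day.
- **Objectives and study aims** asks whether the app is effective and whether it reduces symptoms. **Inclusion criteria** requires a THI of at least 18.

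**The concern.** A multiple-baseline design gains its internal validity while some groups are treated and others are still in baseline. A change that follows each group's own start, rather than the calendar, can then be attributed to treatment. Here that period is short compared with the intervention, and both tests of change look at its far end. By then every group has had the same 12 weeks of treatment.

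The design sentence names no outcome to which it is limited, and the aims are causal. A reader would naturally carry the claimed protection over to the THI and end-of-intervention EMA results. If it does not apply there, a significant paired t-test could reflect drift, natural course, repeated self-rating or regression to the mean after entry on a THI threshold, and still be reported as an effect of the app.

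**Working it through.** **Inputs from the protocol.** 4 groups; successive starts 3 to 5 days apart; first baseline at least 7 days; intervention 12 × 7 = 84 days; minimum sample 20.

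**The plan's own figure.** 4 groups × 5 participants = 20, as stated under Target sample size.

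**Span of the stagger.** Four starts cannot all lie within 3 to 5 days of one another: three gaps of at least 3 days already put the first and last 9 days apart. The rule must therefore refer to successive starts.

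| Gap | First to last start | Share of 84 days | Last start, if first baseline is 7 days | Treated days of first group with no group left in baseline |
|---|---|---|---|---|
| 3 days | 3 × 3 = 9 | 9/84 = 10.7% | after day 7 + 9 = 16 | 84 − 9 = 75 |
| 5 days | 3 × 5 = 15 | 15/84 = 17.9% | after day 7 + 15 = 22 | 84 − 15 = 69 |

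A longer first baseline shifts the start days but not the span.

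**What the paired t-tests do under drift alone.** Assume no treatment effect, n = 20, two-sided alpha 0.05 (the protocol states none), and a mean time drift of d SDs of the paired difference. The test statistic is then noncentral t with 19 df and noncentrality d√20. The critical value is 2.093.

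| d (assumed) | d√20 | Rejection rate |
|---|---|---|
| 0.2 | 0.89 | 14% |
| 0.3 | 1.34 | 25% |
| 0.5 | 2.24 | 56% |
| 0.8 | 3.58 | 92% |

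**Can differences in interval length rescue the before-after contrast?** With a 7-day first baseline, the pre-post interval is 7 + 84 = 91 days in the first group and 100 (3-day gaps) to 106 (5-day gaps) in the last. Fit change = treatment + slope × days, with 5 per group. The SE of the treatment term, relative to the unadjusted mean change, is √(1 + mean²/variance) of the interval.

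- 3-day gaps: mean 95.5, variance 11.25; √(1 + 95.5²/11.25) = 28.5.
- 5-day gaps: mean 98.5, variance 31.25; √(1 + 98.5²/31.25) = 17.6.

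Even for purely linear drift, the SE is multiplied by about 18 to 28.

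**Can daily EMA rescue the late effect?** After the last start, groups still differ in days of exposure on the same study day. A least-squares model with group, study-day and separate exposure-day effects has full rank, so the mean effect over the last treated week is estimable. This needs day effects common to all groups and an exposure effect common to all groups. With an assumed daily SD of 15 VAS points, independent days and 5 per group, its SE is 29.7, 21.9 and 17.3 points for gaps of 3, 4 and 5 days. The SE scales with the SD: about 12 to 20 points for an SD of 10, and 23 to 40 for an SD of 20. On a scale from 0 to 100 this is uninformative.

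**The case against.** **The design sentence is general and modest.** It speaks of enhancing validity and names neither the THI nor end-of-intervention EMA. Both analysis lines openly describe before-after change, and the study calls itself a pilot. Plotted EMA courses are a usual way to read a multiple-baseline design. All of this is fair, and it makes the problem one of scope rather than a direct contradiction. It does not remove it: nothing in the text restricts the claim, and the only tests listed for change over the study fall outside what the stagger protects.

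**The SAP is not shown.** The randomised starts would permit a start-point randomisation test, and an SAP may contain one. That would help with EMA change near the phase change. It could not help the THI, which has two time points, and it could not create an untreated group at week 12.

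**Stronger readings.** A reader might infer that no analysis could separate treatment from time for late EMA. That is not correct: the exposure-day model identifies a late effect, though far too imprecisely to use. A reader might also infer that the staggered window is too weak to show anything, by setting a small difference expected under gradual accrual beside the SE of a phase effect. The protocol gives no onset profile, effect size or SD, and an SE for an immediate step effect cannot be compared with a difference that assumes slow linear accrual. Nor do the documents support rejecting the design: an abrupt EMA change at the start of treatment is what it is suited to detect.

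**Conclusion.** The point holds for the two contrasts that are tested. The stagger spans 9 to 15 of 84 days, the tests do not use it, the THI is never taken within it, and no group is untreated at the end. All of this follows from the protocol's own timings, without any assumption about effect size. As planned, the THI and end-of-intervention EMA results are uncontrolled before-after estimates.

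The rejection rates of 25% and 56% are illustrations. They rest on the assumed alpha and on drifts of 0.3 and 0.5 SD, and the true drift is unknown. The late-effect SE of about 17 to 30 points rests on the assumed SD of 15, independent days and additive effects.

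The point does not extend to EMA change at or soon after each start, where the randomised stagger can support a causal statement. It should be corrected because it limits what the trial may conclude.

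**What to change.** 1. **Study design:** limit the internal-validity statement to EMA change at or soon after the phase change.
2. **Statistical analysis:** base any causal statement on an EMA comparison that uses the randomised starts, for example a start-point randomisation test. If the SAP already contains one, refer to it here.
3. **Statistical analysis and reporting:** label the baseline-to-end EMA change and the pre-post THI change as uncontrolled before-after estimates, and report them with confidence intervals.

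The protocol lists the trial as completed, so the schedule cannot change. None of these steps needs new data: the cost is rewording and one analysis of EMA data already planned for collection. The downside is a weaker efficacy statement, since the 12-week results could no longer be presented as protected against time effects.

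### The EMA paired t-test uses only participants still making app entries at the end of 12 weeks, although app compliance is itself a study aim

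*Protocol*

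**What the plan says.** Under Objectives and study aims, the protocol sets two questions side by side: "On the one hand, treatment compliance and app use is being investigated", and then "it will be investigated whether the tinnitus symptoms are reduced by the app intervention". The same paragraph states where the diary data come from: "The UNITI app consists of structured tinnitus counseling, acoustic therapy and an Ecological Momentary Assessment (EMA) module". Under Outcome measures, tinnitus distress and loudness are rated daily on 0 to 100 scales through both phases. The THI is listed as a separate method: "Clinical questionnaire (applied before baseline phase and after intervention phase".

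The Statistical analysis list gives one test of change for each source:

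- "EMA: paired t-test to determine change from baseline phase to end of intervention phase"
- "THI: paired t-test to determine change from pre baseline phase to post intervention phase"

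It also plans plots of the symptom courses, the distress-loudness relationship over the study, a comparison of THI with EMA distress, and "Descriptive statistics for demographics, tinnitus characteristics and app use". The target is "minimum 20 participants (to allocate at least 5 participants to each group". The intervention lasts 12 weeks in all groups, after a baseline of at least 7 days.

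**The concern.** A paired t-test works on one difference per person. Without a second value there is no difference, and the person leaves the test. For EMA the second value is an app entry at the end of the intervention phase, so leaving the app and leaving the test are the same event. Someone who completes the baseline and eight weeks of intervention entries, then stops, adds nothing to the EMA change test.

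This would matter little if the test needed only data that everyone supplies. Here the study is remote, each person is followed for about three months or more, and the protocol expects enough variation in use to make compliance a research question. If people who do not benefit tend to stop, the reported mean improvement is too favourable. If people who feel better tend to stop, it is too unfavourable. In either case the pilot's conclusion on effectiveness would describe a self-selected subset.

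**Working it through.** **The plan's own figure.** 4 groups × 5 participants = 20, which matches the stated minimum. It is an allocation minimum. The protocol gives no SD, alpha, power or dropout rate, so everything below rests on assumed ranges.

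**Length of follow-up.** Assume the first group has the minimum 7-day baseline. It is then followed for 7 + 84 = 91 days. The fourth group starts the intervention three gaps of 3 to 5 days later, so its total is 91 + 9 = 100 to 91 + 15 = 106 days. An EMA end value requires app use up to that point.

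**Step 1: pairs left.** With proportion d stopping before the end, 20 × (1 − d) pairs remain.

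**Step 2: mean over all allocated.** This is (1 − d) × mean change in stayers + d × mean change in those who stopped. Assume stayers improve by 10 points. The arithmetic is the same on either scale, and the paired t-test reports 10 in every row.

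**Step 3: bias under a selection model.** Suppose change and the tendency to stay are bivariate normal with correlation ρ. The bias of the complete-pair mean, in SDs of change, is ρ × φ(z) / (1 − d), where z is the d-quantile of the standard normal. For d = 0.4, φ(z) / (1 − d) = 0.644, so ρ = 0.2 gives 0.13 and ρ = 0.6 gives 0.39.

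**Step 4: precision.** Solve P(T > t(0.975, n − 1)) = 0.80 for the standardised paired effect, where T is noncentral t with n − 1 degrees of freedom and noncentrality effect × √n. Two-sided 0.05 and 80% power are assumed. With all 20 pairs the detectable effect is 0.660.

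| d | Pairs | All-allocated mean, those who stopped change 0 | Same, they improve by 5 | Bias in SD, ρ = 0.2 to 0.6 | Detectable effect |
|---|---|---|---|---|---|
| 0.2 | 16 | 8 | 9 | 0.07 to 0.21 | 0.749 |
| 0.3 | 14 | 7 | 8.5 | 0.10 to 0.30 | 0.810 |
| 0.4 | 12 | 6 | 8 | 0.13 to 0.39 | 0.889 |
| 0.5 | 10 | 5 | 7.5 | 0.16 to 0.48 | 0.996 |

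**Step 5: the other direction.** With ρ = 0 the bias is 0 in every row. If those who stop have improved more, it reverses. With d = 0.4, stayers at 5 and the others at 10, the all-allocated mean is 0.6 × 5 + 0.4 × 10 = 7, and the test reports 5.

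**Step 6: why THI differs.** The THI has two occasions and no values between them. A repeated-measures model that keeps people with only a pre value estimates the post mean as the completers' post mean + slope × (all-participant pre mean − completers' pre mean). If both pre means are equal, the added term is zero and the model returns the completers' 10, the same as the t-test. Only a stated assumption about the missing values moves the answer: assigning zero change at d = 0.4 gives 0.6 × 10 + 0.4 × 0 = 6. EMA is different because those who stop leave intervention values behind, and a model can use them.

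**The case against.** The strongest reply is that analysis sets and missing-data rules belong in the SAP, which is not at hand. The protocol nowhere says that only complete pairs will be analysed, and a paired t-test can follow imputation. This stands as far as it goes: the absence of a missing-data section is no fault here. It does not answer the point about the stated method. With daily values collected throughout, the protocol names a contrast of baseline with the end of the intervention, and that contrast by itself makes no use of the days between.

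Three stronger readings are tempting, and the document does not support them.

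- A reader might infer that both efficacy tests are confined to people who kept using the app. For THI this does not follow. It is a separate questionnaire, and nothing ties the post-intervention THI to continued app use. Someone who left the app can return it and be counted.
- A reader might infer that the diary days of those who stopped are thrown away. They are unused in the EMA change test only. The plots and the distress-loudness analysis can include them, and the planned description of app use would make non-use visible.
- A reader might infer that the benefit is overstated by a known amount. Every rate and effect in the working is assumed, the direction can reverse, and 20 is a minimum rather than the expected number.

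**Conclusion.** The point holds for EMA. The named test rests on participants still making entries at the end of the 12 weeks, and this selection overlaps with an outcome the trial sets out to study. No figure in the protocol is wrong on this account. The bias is zero if stopping is unrelated to symptom course. Under the assumed dropout of 20% to 50% and correlations of 0.2 to 0.6, it is 0.07 to 0.48 SD of change. The loss of pairs occurs whatever the direction of bias: under the same dropout, 10 to 16 of 20 pairs remain, and the detectable effect rises from 0.660 to between 0.749 and 0.996.

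For THI the point is narrower. The test describes those who returned the post questionnaire, and the reader needs to see who they are. The change is worth making because a better EMA analysis is available from data already collected.

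**What to change.** **EMA.** Make the main change analysis a likelihood-based mixed model, fitted separately to distress and to loudness, on every available daily value from all allocated participants. Use phase and time within phase as fixed effects, participant random effects and serially correlated errors. Estimate the change at the end of the intervention from this model, and report the paired t-test as supplementary.

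**THI.** Keep the paired t-test and say that it covers those who returned the post questionnaire. Report how many lack a post value, and show their baseline THI and baseline-phase EMA beside those of completers. Add a sensitivity analysis that assigns them zero change.

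**Cost.** No new data are needed, which matters because the trial is listed as completed. For the same reason, the report should say that the analysis was changed after data collection had ended. The work is modest. The mixed model relies on a missing-at-random assumption: for those who stopped, the end-of-intervention value is projected from their recorded days, and no off-app EMA exists to check it. The mean change may turn out less favourable than the t-test's.

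### The only named EMA test of symptom change is a before-after paired t-test that does not use the randomised staggered start, so a common time trend enters its estimate in full

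*Protocol*

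**What the plan says.** Under Study design in the Summary, the protocol describes a multiple baseline design across four groups and gives the reason for it: "Staggered introduction of intervention phase to separate treatment effects from random time effects and therefore enhance internal validity". Under Randomization, participants are allocated to groups at random, and "the order of the groups is randomly determined and the start of the intervention phase is randomly determined (Koehler-Levin method"). Baseline lasts at least 7 days, group starts lie 3-5 days apart, and every group then has a 12-week intervention phase. The efficacy question is causal: does the app lower tinnitus symptoms?

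Under Statistical analysis there are four EMA items:

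- plots of the distress and loudness courses;
- "EMA: paired t-test to determine change from baseline phase to end of intervention phase", the one item that names a test;
- an item on how the two ratings relate to each other, with no method named: "EMA: change in relationship between tinnitus distress and loudness over study course";
- a cross-check of the two instruments, again without a method: "Comparison of THI with EMA tinnitus distress".

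None of the four mentions group, start day or study day.

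**The concern.** The design and the test do not match. A paired t-test takes one baseline value and one end value per person. It returns the same p-value whether the starts were staggered, simultaneous or not randomised at all. It is the test of an uncontrolled one-group before-after study.

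Such a test cannot tell the app's effect from anything else that moves ratings over the same weeks. Candidates are present in the protocol itself: entry requires a THI score of at least 18, which invites regression to the mean; participants rate themselves daily throughout, which may change the ratings; and data collection was expected to run from May to October. At the 12-week endpoint no group is still untreated. A significant result could therefore be read as a benefit of the app, with the randomised stagger cited in support, although the stagger played no part in the test.

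**Working it through.** **The plan's own figure.** 4 groups × 5 participants = 20, the stated minimum. This reproduces. The protocol gives no alpha, power, SD or expected effect, so there is no power figure to check.

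**What the stagger provides.** Reading the 3-5 days as the gap between consecutive groups, three gaps give 3 × 3 = 9 to 3 × 5 = 15 days from first to last start. For a fixed first start there are 4! × 3³ = 24 × 27 = 648 group-order and start patterns. Allocating 20 participants to four groups of 5 can be done in 20!/(5!)⁴ ≈ 1.17 × 10¹⁰ ways. A randomisation test is therefore not limited by the number of possible assignments.

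**What the t-test estimates.** Assume the end value is the mean of the last 7 days of the 84-day intervention. With baseline length b, the baseline midpoint is day (b − 1)/2 and the end midpoint is day b + 80, counting from day 0. The distance is 80.5 + b/2 days. For baselines averaging 13 days (7, 11, 15, 19) it is 87 days. Hence

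expected paired change = treatment effect + daily drift × 87.

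With no treatment effect, a drift of 5, 10 or 15 points per 84 days gives 5 × 87/84 = 5.2, 10 × 87/84 = 10.4 and 15 × 87/84 = 15.5 points of apparent change.

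**Exact rejection rates.** For n = 20 and two-sided 5%, with common drift equal to d SDs of the paired change and no treatment effect, the statistic is noncentral t with 19 df and noncentrality d√20:

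| d | 0 | 0.2 | 0.3 | 0.5 | 0.8 | 1.0 |
|---|---|---|---|---|---|---|
| P(reject) | 5% | 14% | 25% | 57% | 92% | 99% |

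**Simulation, assumption set A.** 5 per group, starts after days 7/11/15/19, between-person SD 20, daily within-person SD 15, AR(1) 0.3, person-slope SD 8 per 100 days. No treatment effect (300 runs, 199 permutations; a repeat run with the same SDs in brackets):

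| Common fall per 100 days | Paired t | Randomisation test |
|---|---|---|
| 5 points | 36% (35%) | 3% (about 5-6%) |
| 10 points | 89% (91%) | 5% (about 5-6%) |

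**Simulation, assumption set B.** First baseline 7 days, random gaps of 3-5 days, same between-person and daily SDs, AR(1) 0.4, SD of individual 12-week drift 10 points, randomisation test on the first 36 days, 1000 runs, 199 redraws:

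| 12-week drift, true effect | Paired t | Randomisation test | Mean paired change |
|---|---|---|---|
| 0, none | 6% | 5.0% | +0.1 |
| 5, none | 34% | 5.7% | −5.2 |
| 10, none | 85% | 4.8% | −10.3 |
| 15, none | 99% | 5.2% | −15.5 |
| 0, immediate 10 | 81% | 85% | −9.9 |
| 10, immediate 10 | 100% | 82% | −20.4 |

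The simulated mean changes agree with the formula to within 0.1 point.

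**What the alternative cannot do.** In set A the randomisation test detects an immediate 10-point effect in 65% of trials (paired t: 95%). Across all runs its power for that effect was about 65-88%. For a treatment effect that builds linearly to 10 or 20 points over 84 days, again with set A's SDs, it rejects in only about 3-5%, its null level, while the t-test rejects in about 91-100%.

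**The case against.** **The list of EMA items is wider than one test.** A reader might infer that the t-test is the only EMA test of any kind, or that the daily values between baseline and end go unused. The protocol does not support that. The distress-loudness item has no method named and may involve a test, and the plots use every day's data and can show whether change follows the staggered starts. What stands is narrower: neither the distress-loudness item nor the THI comparison tests the treatment effect, and a plot yields no estimate or error rate.

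**The statistical analysis plan is not at hand.** It may contain a randomisation test or mixed model; naming the Koehler-Levin method makes that plausible. The protocol does not call the t-test primary or exclusive. So one cannot conclude that no design-based analysis was planned, only that the test named in the protocol does not serve the design's stated purpose.

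**Baseline lengths are not fixed.** Seven days is a minimum. Baselines of 7 days in the first group and 16-22 in the last (7 + 9 to 7 + 15) are the shortest case.

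**Replacing the t-test would be costly.** Counselling content runs from basics to advanced topics and sound use is daily, so a slow benefit is plausible, and a test on the starts would very probably miss it. This is a sound argument against replacement. It does not make the t-test causal: with a gradual effect, the 9-15 days of stagger give almost no means of separating treatment from time.

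**It is a completed, retrospectively registered pilot.** That limits what can be changed and argues for an added analysis and cautious wording. It does not remove the mismatch, because the protocol states an efficacy aim and claims enhanced internal validity.

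**Conclusion.** The concern holds in this form: the only named EMA test of symptom change ignores the randomised start, and a common trend passes into its estimate in full. That follows from the form of the test and needs no assumed number.

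The size does depend on assumptions. With 20 participants and the assumed SDs, a pure drift of 5 or 10 points per 100 days gives about 35% or 90% significant results, against about 5% for a randomisation test. The drift, the SDs, the autocorrelation, the 5% level and the last-7-days definition of the end are all assumed. With no drift the t-test stays near 5%. A reader might infer that this trial's EMA result is a false positive; nothing in the protocol says what drift, if any, occurred.

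**What to change.** Under Statistical analysis, add as the basis for any causal statement:

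- a randomisation test of the phase effect on daily EMA distress and on daily EMA loudness, with its reference distribution taken from the participant allocation, group order and start-day scheme actually used;
- a supporting linear mixed model on all daily values with phase, study day, participant random effects and autocorrelated errors.

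Keep the paired t-test, or the mean difference with its confidence interval, but describe it as uncontrolled before-after change and do not attribute it to the app. State that the design cannot separate a gradual 12-week effect from time, since starts differ by only about 9-15 days; a mixed-model term for time since start would be separated from study day only weakly for the same reason. If the analysis is added after data collection, label it as added.

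The cost is analysis work only: the design already supplies daily ratings and random starts. The price in inference is power of about 65-88% for an immediate 10-point effect, depending on assumptions, and almost none for a gradual one. If no design-based analysis is added, the causal wording and the internal-validity claim should not be carried over to the EMA result.
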